## Abstract

**Introduction:**

Nigeria, Ethiopia and Tanzania have some of the highest teenage pregnancy rates and lowest rates of modern contraceptive use among adolescents. The transdisciplinary Adolescents 360 (A360) initiative being rolled out across these three countries uses human-centred design to create context-specific multicomponent interventions with the aim of increasing voluntary modern contraceptive use among girls aged 15–19 years.

**Methods:**

The primary objective of the outcome evaluation is to assess the impact of A360 on the modern contraceptive prevalence rate (mCPR) among sexually active girls aged 15–19 years. A360 targets different subpopulations of adolescent girls in the three countries. In Northern Nigeria and Ethiopia, the study population is married girls aged 15–19 years. In Southern Nigeria, the study population is unmarried girls aged 15–19 years. In Tanzania, both married and unmarried girls aged 15–19 years will be included in the study. In all settings, we will use a prepopulation and postpopulation-based cross-sectional survey design. In Nigeria, the study design will also include a comparison group. A one-stage sampling design will be used in Nigeria and Ethiopia. A two-stage sampling design will be used in Tanzania. Questionnaires will be administered face-to-face by female interviewers aged between 18 and 26 years. Study outcomes will be assessed before the start of A360 implementation in late 2017 and approximately 24 months after implementation in late 2019.

**Ethics and dissemination:**

Findings of this study will be widely disseminated through workshops, conference presentations, reports, briefings, factsheets and academic publications.

Strengths and limitations of this studyThis study is part of an independent multicomponent impact evaluation of a multicountry adolescent sexual and reproductive health intervention, and we will collect comparable data before and after intervention implementation in four different settings in three countries.In Nigeria, the randomisation of intervention allocation was not possible; therefore, in this quasi-experimental design, conclusions about causality are less definitive than a cluster-randomised design.Triangulation with dose–response and trends analyses will strengthen the inference possible from the study findings.Due to resource constraints, we focused resources on selected geographical areas, and we acknowledge that this will restrict the generalisability of our findings.

## Introduction

In 2012, the global community launched the Family Planning 2020 (FP2020) initiative to reach 120 million new contraceptive users in developing countries by 2020.^1^ Specifically, it calls for meeting all women’s needs for modern contraception to prevent unintended pregnancies and reducing the high adolescent birth rates in the world’s poorest countries. Helping adolescent girls avoid unintended pregnancies can have far-reaching benefits for them, their children and societies as a whole.^2^ Complications of pregnancy and childbirth are the leading cause of death among girls aged 15–19 years,^3 4^ and babies born to adolescent mothers face greater health risks than those born to older women.^5^ Moreover, adolescent childbearing is associated with lower educational attainment, and it can perpetuate a cycle of poverty from one generation to the next.^3^

From 1990 to 2010, adolescent fertility rates declined in most countries.^6^ However, adolescent fertility rates remain high in many lower-income countries. In some countries, fertility rates are declining more slowly in adolescents than in older women.^1^ Nigeria, Ethiopia and Tanzania have among the highest rates of adolescent fertility globally, with 109, 57 and 118 births per 1000 girls aged 15–19 per year, respectively.^1^ Equally, these countries also have some of the lowest rates of use of modern contraception in adolescents. In Nigeria, 98.8% of married adolescent girls and 50.3% of unmarried sexually active adolescent girls do not use a modern contraceptive method.^7^ The equivalent figures are 68.2% and 42.5% in Ethiopia^8^ and 86.7% and 66.9% in Tanzania.^9^ Preventing pregnancy among adolescents is a global priority and new interventions are needed, particularly in countries like Nigeria, Ethiopia and Tanzania where adolescent fertility rates remain high.

Despite having clear needs, both married and unmarried adolescent girls in many low-income and middle-income countries lack access to reliable contraception. In addition, rates of contraceptive failure are higher in adolescents than in older women, with younger women more likely to abandon contraception despite ongoing need.^10^ Reasons include poor understanding of pregnancy risks, concerns about the effect of contraceptives on health or fertility and opposition from partners. Lack of knowledge of services, cost, shyness and community stigma about sexual activity and disapproving attitudes from providers are further barriers.^10^ Adolescent sexual and reproductive health is affected by a country’s cultural, religious, legal, political and economic contexts. In responding, health actions are needed at each level, from structural, through to community settings including schools and health services.^4 10^ The most effective programmes are typically multicomponent and target one or more of these settings.^4 10^ There are a range of effective and scalable interventions including comprehensive sexuality education and provision of youth-friendly sexual and reproductive health services. Yet the evidence base for action remains relatively weak.^4 11^ The overwhelming majority of intervention studies derive from high-income countries.^11^

Adolescents 360 (A360) is an initiative in the field of adolescent sexual and reproductive health programming, with the intention of being implemented at scale in Nigeria, Ethiopia and Tanzania. The final package of interventions is country-specific and includes a combination of community-based sexual and reproductive health education, counselling and improved contraceptive provision through ‘adolescent friendly’ services. The external evaluation of the A360 intervention comprises an outcome evaluation, a process evaluation and a cost effectiveness study. We present here the study protocol for the outcome evaluation of A360.

## Methods and analysis

### Study objective

The primary objective of the outcome evaluation is to evaluate the effectiveness of the A360 programme in increasing the uptake of voluntary modern contraception among sexually active girls aged 15–19 years.

### Study settings

In Nigeria, A360 is being implemented by the Society for Family Health (SFH)^12^ in three states in the north (Federal Capital Territory, Nasarawa, Kaduna) and in seven states in the south (Lagos, Osun, Ogun, Oyo, Edo, Delta and Akwa Ibom) of the country. The A360 programme will be implemented in approximately 60% of the local government areas (LGAs) in each selected state. We will conduct the outcome evaluation in four LGAs in Nasarawa State and two LGAs in Ogun State. Nasarawa State is a state in north central Nigeria with a total population of 1.9 million.^13^ Overall, 41.3% of the female household population have no education, and the median age at first marriage for women is 19.7 years.^7^ Current use of modern contraception among married women aged 15–49 years is 16.3%. Ogun State in south western Nigeria has a total population of 3.8 million.^13^ Overall, 24.1% of the female household population have no education, and the median age at first marriage for women is 20.5 years. Current use of modern contraception among married women aged 15–49 years is 21.5%.^7^

In Ethiopia, A360 is being implemented by Population Services International (PSI) in two city administrations and five regional states (Addis Ababa, Amhara, Dire Dawa, Harari, Oromia, Southern Nations, Nationalities and People’s Region and Tigray). Within each of the selected regional states, A360 will be implemented in selected woredas (districts), and we will conduct the outcome evaluation study in four woredas in Oromia Region. Oromia Region has a total population of 27 million.^14^ Overall, 51.5% of the female household population have no education, and the median age at first marriage for women is 17.4 years. Current use of modern contraception among married women aged 15–49 years is 28.1%.^8^

In Tanzania, A360 is being implemented by PSI in 10 regions (Kagera, Geita, Mwanza, Arusha, Tabora, Tanga, Dar es Salaam, Mbeya, Iringa and Morogoro). We will conduct the outcome evaluation in urban and semiurban wards of Ilemela District, Mwanza Region. Mwanza Region has a total population of 2.8 million.^15^ Overall, 24.2% of the female household population have no education, and the median age at first marriage for women is 18.9 years. Current use of modern contraception among married women aged 15–49 years is 18.4%.^9^

### Interventions under study

The A360 interventions are being designed using a human-centred design process which includes the following steps^16^:Inspiration: a period of formative research to understand adolescent girls’ sexual and reproductive health needs and their sociocultural environment.Ideation: an iterative process of generating, testing and refining ideas and developing and testing prototypes in real-world settings.Implementation: intervention rollout at scale in target regions across the three countries.

Interventions are currently in the final round of prototyping (ideation phase). The most likely final package of interventions in each setting is described in table 1.

**Table 1 T1:** The likely final A360 package of interventions in each setting

A360 country	Target population	Intervention
Nigeria (North)	Married girls	Under design at the time of writing. Due to security issues during the design phase, it was not feasible to develop a context specific programme. A rapid assessment based on insights and prototypes from the other contexts is underway to determine the programme to rollout in Northern Nigeria.
Nigeria (South)	Unmarried girls	***‘****9ja Girls****’*** Mobilisation of girls aged 15–19 to attend 9ja Girls events by emphasising vocational skills and life planning. Sensitisation sessions in the community with mothers. Community launches involving key community influencers (eg, local government, religious leaders). Physical (eg, in a public health centre) and digital (eg, online forums) safe spaces for girls. Public health centre-based vocational skills classes focusing on job skills and life planning, including opt-out one-to-one counselling sessions with adolescent friendly providers to address fears, dispel myths and highlight benefits of contraception. Opt-out means that girls will be counselled by a service provider unless they decline. Public health centre-based delivery of family planning products and/or referral to adolescent friendly providers. ***‘****9ja Girls****’*** will use clusters of public health centres, private social-franchise clinics and stand-alone clinics in facilities donated by the Ministry of Health.
Ethiopia	Married girls	***‘****Smart Start****’*** Community-based financial planning linked to family planning counselling sessions for newly married or soon to be married couples/girls to enable informed choice and decision making. Delivered in partnership with the national Health Extension Programme via Health Extension Workers and augmented by the existing community infrastructure of the Women’s Development Army and a PSI-recruited *‘Smart Start’* team and local Youth Champions. Delivery of family planning products through local service providers.
Tanzania	Unmarried and married	***‘****Kuwa Mjanja****’*** (Be Smart) Mobilisation of girls aged 15–19 to attend *‘Kuwa Mjanja’* events by emphasising vocational skills, learning about body changes and/or planning for life goals. Community and clinic-based events for mothers to sensitise them to their daughters’ developmental stages associated with the desire to use contraception to prevent unwanted pregnancy in adolescent girls. Pop-up and clinic-based events focusing on vocational skills and life planning for girls, including opt-out one-to-one counselling sessions with adolescent friendly providers to address fears, dispel myths and highlight benefits of contraception. Opt out means that girls will be counselled by a service provider unless they decline. Community-based and clinic-based delivery of family planning products. Sustained interaction and engagement through *‘Kuwa Mjanja’* branded clubs and social media forums. Club-based events focusing on vocational skills, learning about their bodies, reproductive health and contraception. ***‘****Kuwa Mjanja****’*** will use both public and private social-franchise clinics in partnerships with the Ministry of Health, NGOs and community-based organisations.

A360, Adolescents 360; PSI, Population Services International.

### Design of outcome evaluation

A summary of the methods used can be found in table 2. Separate protocols were developed for each country to take into account the country-specific A360 implementation strategies and study designs developed.

**Table 2 T2:** Summary of methods

A360 country	A360 regions	Study design	Outcome evaluation study setting	Study population (sample size)	Sampling strategy
Nigeria (South)	Lagos, Osun, *Ogun*, Oyo, Edo, Delta, Akwa Ibom	Cross-sectional before-and-after study with comparison group	Ogun State: Ado-Odo Ota LGA (intervention) Shagamu LGA (comparison)	Unmarried girls aged 15–19 years (12 020) Cohabiting adults (250)	Single stage cluster design PSU: EA Simple random sample of EAs (approx. 710 in Ogun). All HHs visited in selected EAs. All eligible individuals to be recruited to participate.
Nigeria (North)	Federal Capital Territory, Kaduna, *Nasarawa*	Cross-sectional before-and-after study with comparison group	Nasarawa State: Doma LGA (intervention) Toto LGA (comparison) Karu LGA (intervention) Nasarawa LGA (comparison)	Married girls aged 15–19 years (4555) Husband (250)	Single stage cluster design PSU: EA Simple random sample of EAs (approx. 1150 in Nasarawa). All HHs visited in selected EAs. All eligible individuals to be recruited to participate.
Ethiopia	Addis Ababa, Amhara, Dire Dawa, Harari, *Oromia*, SNNP, Tigray	Cross-sectional before-and-after study	Oromia regional state: Wara Jarso, Lome, Ada’a, Fentale woredas	Married girls aged 15–19 years (1926) Husband (128)	Single stage cluster design PSU: Kebele Probability proportional to size sample of 45 kebele. All HHs visited in selected kebele. All eligible individuals to be recruited to participate.
Tanzania	Kagera, Geita, *Mwanza*, Arusha, Tabora, Tanga, Dar es Salaam, Mbeya, Iringa, Morogoro	Cross-sectional before-and-after study	Mwanza region: Ilemela district (urban and semiurban wards only)	Married and unmarried girls aged 15–19 years (4980) Cohabiting adults (127)	Two stage cluster design PSU: Street Simple random sample of 30 streets. Simple random sample of 50 GPS points within each street. All HHs with front door within 20 m radius of GPS point visited. All eligible individuals recruited to participate.

A360, Adolescents 360; EA, enumerations area; GPS, Global Positioning System; HH, household; LGA, local government area; PSU, primary sampling unit; SNNP, Southern Nations, Nationalities and People’s Region.

#### Nigeria

The intervention will be evaluated in Ogun (South Nigeria) and Nasarawa (North Nigeria) through population-based surveys conducted at baseline (late 2017) and approximately 24 months after the start of the intervention. In Nasarawa, four LGAs consisting of two similar pairs have been selected for evaluation. Two of these will receive the intervention (one in each pair) and two will not, that is, they will act as comparisons. In Ogun, the evaluation will be conducted in only two LGAs (one intervention and one comparison).

##### Study unit inclusion criteria and selection

Study states were selected by SFH. The selected states were chosen because of the absence of other large-scale adolescent focused sexual and reproductive health activities and because of SFH’s previous experience working in these states.

Study LGAs were selected by SFH in collaboration with the state Ministry of Health and local government officials. The LGAs were selected from among those where there were no security concerns, and comparison-intervention pairs were selected to be similar with respect to as many as possible of the following criteria:Population density.Estimated modern contraceptive prevalence rate (mCPR) among 15–49 year olds (DHIS2, 2016).^17^
Number of health facilities.Presence of World Bank support for Maternal and Child Health activities.

##### Allocation to intervention and comparison arms

Within a pair, allocation of an LGA to the intervention or comparison arm of the outcome evaluation study was done by SFH in collaboration with the state Ministry of Health and local government officials.

#### Ethiopia

The intervention will be evaluated through two population-based cross-sectional surveys, one conducted before implementation (late 2017) and another approximately 24 months after the start of the intervention.

##### Study unit inclusion criteria and selection

The study region and woredas were selected by PSI. Oromia region was selected because of its relatively low mCPR as compared with other regions in the Ethiopia Demographic and Health Survey (DHS) 2011 (24.9%) and its standing as having the highest unmet need for contraception (29.9%) as compared with other regions.^18^ Criteria used by PSI for selecting woredas for inclusion in the study included:Good infrastructure and accessible all year round.Close proximity to PSI head office in Addis Ababa.Population of married adolescent girls anticipated to be large.

#### Tanzania

As in Ethiopia, the intervention will be evaluated through before-and-after population-based surveys that are scheduled to take place in late 2017 and approximately 24 months after the start of the intervention.

##### Study unit inclusion criteria and selection

Mwanza Region was selected by the evaluators in collaboration with PSI because of the high unmet need for modern contraception among girls aged 15–19 years relative to other A360 target regions,^9^ the absence of other large-scale sexual and reproductive health activities and because PSI has previous experience working in the region. The study will be restricted to urban and semiurban wards in Ilemela District, in part because PSI focuses efforts in more densely populated areas and in part because of resource constraints.

### Study population

A360 targets different subpopulations of adolescent girls in the three countries (table 2).

#### Inclusion criteria

Adolescent girls aged 15–19 years:Unmarried (Tanzania and Southern Nigeria only).Married or living as married (Ethiopia, Tanzania and Northern Nigeria only).Living, at the time of the survey, in the study sites.Voluntarily provides informed consent.

#### Exclusion criteria

There were no specific exclusion criteria.

### Sampling strategy

A one-stage cluster sampling design will be used in Nigeria and Ethiopia. A two-stage cluster sampling design will be used in Tanzania. In each country, we will use the smallest available administrative unit as the primary sampling unit. Specifically, we will use enumeration areas (EAs) from the 2006 census in Nigeria, kebele from the 2007 census in Ethiopia and streets in Tanzania.

#### Nigeria

The Nigeria Population Commission maintains a database of about 600 000 EAs across the entire country, which shows that EAs in Nasarawa have an average of 44 households and EAs in Ogun have an average of 52 households. They advised us that EA population counts are considered unreliable, which creates issues when using proportional to population size sampling techniques. To overcome this issue, we will use a simple random sample of EAs. To maximise the efficiency, in terms of logistics, of the study, we will sample clusters of approximately 100 households. Thus, if a selected EA contains fewer than 100 households, then we will randomly sample one of the neighbouring EAs and enumerate all households in that EA. If 100 households are still not enumerated, then a further additional EA will be randomly sampled and enumerated. We estimate that, using this technique, a simple random sample of approximately 710 EAs in Ogun and 1150 EAs in Nasarawa will need to be selected to reach the target sample size of adolescent girls. All eligible unmarried girls aged 15–19 years in the selected households in Ogun and all eligible married girls aged 15–19 years in Nasarawa will be recruited to participate in the structured interview. In Nasarawa, in order to reach our target sample size of 250 husbands, we estimated that for every 17 sexually active married girls interviewed, one will be systematically selected and asked permission to interview her husband. In Ogun, due to the uncertainty in the proportion of unmarried girls who will report that they are sexually active, we propose that for every 7–14 sexually active unmarried girls surveyed, one will be systematically selected and asked permission to interview a cohabiting adult in order to reach our target sample size of 250 cohabiting adults. The exact sampling interval will be finalised following the pilot study.

#### Ethiopia

A sample of 45 kebeles will be selected from across the four study woredas with probability proportional to population size. Within the selected kebele, we will visit each household and all eligible married girls aged 15–19 years will be recruited to participate in the structured interview. In households that have more than one eligible married female aged 15–19 years, all consenting married adolescent girls will be interviewed. In order to reach our target sample size of 128 husbands, we estimated that for every 15 sexually active married adolescent girls aged 15–19 years interviewed, one will be systematically selected and asked permission to interview her husband.

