#### Tanzania

A simple random sample of 30 ‘streets’ (neighbourhoods) will be selected from across the 15 urban and semiurban wards of Ilemela District. The boundaries of each selected street will be identified and mapped using Global Positioning System (GPS) devices,^19^ and within each street, we will randomly select 50 GPS coordinates using ArcGIS software V.9.3 (Esri, Redlands, USA).^20^ All households whose front doors are located within a radius of 20 m around the GPS point will be visited and all eligible consenting girls aged 15–19 years residing in these households invited to be interviewed. We aim to interview 166 girls per street. In order to reach our target sample size of 127 cohabiting adults, we estimated that for every 10 sexually active adolescent girls aged 15–19 years interviewed, one will be systematically selected and asked permission to interview her husband (married girls) or a cohabiting adult (unmarried girls).

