#### Nigeria

In Ogun State, among sexually active unmarried girls aged 15–19 years, we assumed that between 2017 and 2019, mCPR will increase from 64.4% to 65.6% in the absence of A360 and from 64.4% to 72.6% in the presence of A360. Based on these assumptions and those in tables 4 and 5, our target sample size is 12 020 unmarried girls aged 15–19 years.

**Table 4 T4:** Assumptions for key parameters required for sample size calculations

Parameter	Ogun* (%)	Nasarawa* (%)	Oromia† (%)	Mwanza‡ (%)
Proportion of 15–19-year-old girls who are married (or living together)	10	15	20	22
Proportion of 15–19-year-old girls who are unmarried (not currently married)	90	85	80	78
Proportion of unmarried 15–19-year-old girls who report sexual activity in the past year	15	15	–	25
Proportion of married 15–19 year olds who report sexual activity in the past year	97	97	97	97
Proportion of sexually active girls who are married	42	53	–	52
Proportion of sexually active girls who are unmarried	58	47	–	48
Proportion of households with resident who is female aged 15–19 years	19	29	27	34

Sources:

*Nigeria DHS 2013,^7^ Nigeria GHS 2016.^13^

†Ethiopia DHS 2011,^18^ Ethiopia Mini DHS 2014,^24^ Ethiopia census 2007.^14^

‡Tanzania DHS 2015–2016,^9^ Tanzania census 2012.^15^

DHS, Demographic and Health Survey.

**Table 5 T5:** Sample size estimates

Parameter	Ogun	Nasarawa	Oromia	Mwanza
Target sample of sexually active 15–19 year olds*	1413	3586	1132	1217
Total sample of all 15–19 year olds* Includes non-sexually active girls Taking into account 10% non-response	10 362	4067	1284	3314
Design effect	1.16	1.12	1.50	1.50
Sample size for survey†	12 020	4555	1926	4980

*Includes unmarried girls (Ogun); married girls (Nasarawa and Ethiopia); unmarried and married girls (Mwanza).

†Total sample of all 15–19 year olds × design effect.

In Nasarawa State, among sexually active married 15–19 year olds, we have assumed that between 2017 and 2019, mCPR will increase from 3.0% to 3.1% in the absence of A360 and from 3.0% to 5.1% in the presence of A360. Thus, 4555 married girls aged 15–19 years must be surveyed to achieve 90% power (table 5).

In addition, a sample of 250 cohabiting adults (Ogun) and 250 husbands/male partners (Nasarawa) will be interviewed.

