#### Ethiopia

In Oromia Region, among sexually active married girls aged 15–19 years, we have assumed that between 2017 and 2019, mCPR will increase from 44.0% to 50.8% in the presence of A360. Based on this assumption and those in table 4, 1926 married girls aged 15–19 must be surveyed to achieve 90% power (table 5). In addition, a sample of 128 husbands/male partners will be interviewed.

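### In Oromia, selecting 1 in 15 sexually active married girls interviewed yields about 113 to 125 husbands, not the stated 128; in Nasarawa, 1 in 17 reaches 250 only if the planned non-response does not occur

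*Protocol article*

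**What the plan says.** The Ethiopia part of Sampling strategy links a target of 128 husbands to a selection interval: "we estimated that for every 15 sexually active married adolescent girls aged 15–19 years interviewed, one will be systematically selected". The chosen girl is then approached for consent: "one will be systematically selected and asked permission to interview her husband". The Ethiopia part of Sample size repeats the number as a plain statement: "In addition, a sample of 128 husbands/male partners will be interviewed".

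The Nigeria part of Sampling strategy does the same for Nasarawa, with 250 as the target: "we estimated that for every 17 sexually active married girls interviewed, one will be systematically selected".

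Table 4 has a row headed "Proportion of married 15–19 year olds who report sexual activity in the past year", with 97% for both Nasarawa and Oromia. Table 5 gives, for Oromia and Nasarawa respectively:
- sexually active girls: 1132 and 3586
- totals that allow for girls not sexually active and for 10% non-response: 1284 and 4067
- design effects: 1.50 and 1.12
- survey sizes: 1926 and 4555

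**The concern.** The interval applies to girls who are both interviewed and sexually active. The Oromia survey size of 1926 is larger than that group: it includes girls assumed not to be sexually active and, by the Table 5 row label, an allowance for non-response. Dividing 1926 by 15 gives the target almost exactly, which suggests that the interval was set on the wrong base.

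The number selected is also a ceiling on the number interviewed. The girl must give permission, and the Informed consent section requires consent from every participant, so the husband must agree too. If the ceiling is already below 128, any refusal or absence widens the gap.

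What is at stake is modest: a stated sample size that its own selection rule does not deliver. There is also a practical risk. If a shortfall were noticed during fieldwork and the interval shortened partway, selection probabilities would differ between areas visited early and late. The article does not say that this would be done.

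**Working it through.** **Inputs.** Targets and intervals come from Sampling strategy (Oromia 128, 1 in 15; Nasarawa 250, 1 in 17). Sexual activity among married girls is 97% (Table 4). The sexually active samples, design effects and survey sizes come from Table 5.

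**Step 1: rebuild the survey sizes, to see what they contain.**
- Oromia: 1132/0.97 × 1.1 = 1284, and 1284 × 1.50 = 1926. Matches Table 5.
- Nasarawa: 3586/0.97 × 1.1 = 4067, and 4067 × 1.12 = 4555. Matches Table 5.

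Both survey sizes therefore contain the 3% not sexually active and a 10% addition for non-response.

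**Step 2: reproduce the stated 128.**
- 1926/15 = 128.4. This needs every one of the 1926 girls to be both interviewed and sexually active.

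**Step 3: apply the Oromia rule as written.** Number selected = (sexually active girls interviewed)/15.
- All 1926 interviewed: 1926 × 0.97 = 1868, and 1868/15 = 124.5. Short by 3.5 (2.7%).
- Net of planned non-response: 1132 × 1.50 = 1698, and 1698/15 = 113.2. Short by about 15 (12%).

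**Step 4: the same for Nasarawa.** Number selected = (sexually active girls interviewed)/17.
- All 4555 interviewed: 4555 × 0.97 = 4418, and 4418/17 = 259.9. This is 10 above target and allows for 1 − 250/259.9 = 3.8% refusal.
- Net of planned non-response: 3586 × 1.12 = 4016, and 4016/17 = 236.3. Short by about 14 (5.5%).

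**Step 5: the interval each target needs with no refusals** (sexually active girls interviewed divided by target, rounded down).

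| Setting | All interviewed | Net of non-response |
|---|---|---|
| Oromia | 1868/128 = 14.6, so 1 in 14 | 1698/128 = 13.3, so 1 in 13 |
| Nasarawa | 4418/250 = 17.7, so 1 in 17 | 4016/250 = 16.1, so 1 in 16 |

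The Nasarawa interval thus agrees with a base of all girls surveyed × 97%. The Oromia interval does not: 14.6 would have to be rounded up to give 15.

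**The case against.** The strongest reply is that the survey sizes mean girls interviewed, not girls approached. The Sample size section says that these numbers must be surveyed, and in Tanzania the aim of 166 interviews in each of 30 streets gives 30 × 166 = 4980, exactly the Table 5 survey size. On that reading the lower figures (113 and 236) fall away, Nasarawa meets its target before refusals, and Oromia misses by only 3.5 husbands in a sentence that calls the interval an estimate. For a proportion near 50% under simple random sampling, the 95% half-width would be about 8.8 percentage points instead of 8.7, and 9.2 even at 113. This stands as a limit on the size of the problem. It does not remove the Oromia miss, which remains on either reading.

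A reader might infer more than the article supports:
- **That Nasarawa cannot reach 250.** It can, with about 260 selected if all 4555 are interviewed.
- **That Ogun also fails.** At 15% sexual activity, 1 in 7 selects 12 020 × 0.15/7 = 258 if all are interviewed and 1413 × 1.16/7 = 234 net of non-response. The article gives a range of 7 to 14 and leaves the exact interval until after the pilot, so nothing is yet fixed wrongly.
- **That Mwanza is short.** On Table 5, 1217 × 1.50/10 = 183 are selected for a target of 127. A figure of 122 arises only by taking 1217 as the count of sexually active girls among the 4980, which leaves out the design effect.
- **That refusers will not be replaced.** The article is silent. It condenses separate country protocols and a supplementary file, where such rules would normally be found.

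The sentence about settling the interval after the pilot follows the Ogun text, so it may not cover Nasarawa. The article has no equivalent sentence for Ethiopia.

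**Conclusion.** The point holds for Oromia and conditionally for Nasarawa. In Oromia the stated interval selects about 125 husbands at best and about 113 if the planned non-response occurs, against 128, before any refusal. In Nasarawa, 1 in 17 falls short (about 236 of 250) only if the planned non-response occurs; otherwise the margin covers about 4% refusal.

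The figures rest on the 97% in Table 4 and, for the lower values, on treating the Table 5 non-response allowance as girls who are not interviewed. No refusal rate is given for husbands, and none is assumed here.

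Severity is minor. No power or precision aim is attached to the husband interviews, and the primary outcome does not depend on them.

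**What to change.** Before fieldwork, either:
- recompute the Oromia interval as (sexually active girls expected to be interviewed) × (1 − assumed refusal)/128, state the refusal assumption, and keep the interval fixed throughout. With no refusals this is 1 in 14 if all 1926 are interviewed and 1 in 13 net of non-response; any assumed refusal makes it shorter; or
- keep 1 in 15 and restate the expected number in both Ethiopia sections as about 113 to 125 before refusals.

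Check Nasarawa on the same base: 1 in 16 net of non-response, shorter with any assumed refusal. State whether the Table 5 survey sizes count girls approached or girls interviewed, since this decides which figure applies.

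The cost is a change of wording and of one setting in the selection procedure. If 1 in 13 is used and all 1926 girls are interviewed, 1868/13 = 144 husbands would be selected, about 19 more than under 1 in 15.
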